**Study Population**

Participants will be recruited from Memorial Hermann Hospital patients aged 16 to 35 who presented for a gunshot injury from community-based firearm violence. This age range is selected to capture those with the highest risk for violent victimization incidents. Exclusions will be made for self-inflicted gunshots as the source of firearm injuries.

**Eligibility Criteria**

We will include victims of firearm violence presenting to Memorial Hermann Hospital during the study period, who are English and Spanish speaking and between the ages of 16-35 years old. Exclusion criteria are if they are under the age of 16 or above the age of 35, presenting for a firearm injury that is the result of a self-harm attempt, or unintentional injury, lives outside of Harris County at the time of enrollment, actively detained by the criminal justice systems at the time of enrollment, or if they are non-English (other than Spanish) or non-Spanish speaking(other than English) (meaning we will only include patients who can speak either English or Spanish).

**Age limits**

Min: 16 Max: 35

**Inclusion of individuals across the lifespan**

Our study population will be victims of firearm violence, ages 16 to 35 years, as these are the ages of highest firearm violence, as indicated by data from Memorial Hermann Hospital. We will also identify special populations, including parents, women, minorities, or active duty military/veterans, through our data collection process. We will also exclude incarcerated individuals.

**Inclusion of Women and Minorities**

With the written informed consent from the parents/LARs and child assent, we will enroll children ages 16 and 17 as they have one of the highest rates of firearm violence. We will enroll both male and female study participants. However, we recognize that firearm violence is more common among males and thus the study sample is expected to skew heavily toward males. In addition, we will recruit across all racial and ethnic groups. However, because firearm violence is more common among African American and Hispanic persons relative to White individuals, we anticipate the sample to be more highly composed of Black and Hispanic persons, and anticipate no challenges related to being able to recruit a sample inclusive of minority populations.

We plan to recruit participants from Memorial Hermann Hospital who meet eligibility criteria and who consent to participate in the study according to the study timeline. All initial study contacts will be done via research staff during the hospital presentation. Case managers will provide regular contact using motivational interviewing techniques to maintain enrollment in the program. Gift cards will be utilized to incentivize study retention.

**Data and Safety Monitoring**

Any potential risk to the participant will be minimized by strictly adhering to the research protocol, as approved by the IRB at UTHealth and DHHS for the Protection of Human Subjects. Participants will be informed of the study and risks to participants and will give consent before participation. Participants will be informed that this is voluntary and they can withdraw from the study anytime. No physical or psychological adverse effects of the intervention are known or anticipated. There is minimal incremental risk beyond the risks that are associated with the individual components of the HVIP and enhanced services.  Research related risks are limited and include time spent completing the surveys and potential distress caused by completing the survey.  Processes are in place for study participants to discuss any distress with their case manager, and they can be referred to community support services as needed.

Risks to Human Subjects: All subjects will give informed consent before study enrollment.

Adequacy of Protection Against Risks: Research staff will undergo training in informed consent, and the survey will feature written informed consent before initiating the survey. All aspects of the study will receive IRB approval before initiation. This study does not involve fetuses, or neonates. We will not be asking about pregnancy status in this study.

Potential Benefits of the Proposed Research to Research Participants and Others: There are potential benefits to the participant in the study, with the enhanced services in case management and connection to community-based resources. Studies from previous HVIP interventions have demonstrated significant decreases in re-injury, and thus there is potential for decreased violent re-injury to the patient enrolled in the study.

Importance of Knowledge to be Gained: Understanding the benefit of HVIP to the community and its role in implementing HVIP will be important to the larger firearm violence research networks as a whole. The results of this program can serve as a model of other programs established in hospital systems as a means to curtail violence. If successful, the program can be maintained in the hospital system and will continue to yield benefits in reducing violence in Houston after the study period has ended.

A Data Safety and Monitoring Board (DSMB) will be convened for this study. The DSMB will review the study protocols and provide oversight of recruitment progress, data quality and completeness, efficacy monitoring, and participant safety as it pertains to the study. The research team will be responsible for providing study protocols, data and adverse event reports to the DSMB. All recruitment and data collection will be conducted in Houston, Texas. A formal independent board of experts including investigators and at least one biostatistician will be appointed to the DSMB. The Board will meet annually (at a minimum) to review adverse event data, other safety data, quality and completeness of study data, and enrollment data to ensure proper trial conduct. Our study team will provide any new literature particularly pertinent to the trial, along with their recommendation as to whether it affects the trial conduct or design. The DSMB will review the consent form at regular intervals to determine whether the consent form requires revision in light of any new findings or amendments. All events will be evaluated by the DSMB in accordance with its charter and review procedures (which will be reviewed with the Chair and Members at the initial meeting). This includes an assessment of expectedness, relationship to the study product or procedures, and severity. The study investigators will rely on the DSMB to identify conditions or events that would trigger further action, including a temporary halt, modification, or termination of the study for safety reasons.

**Data Management**

Drs. [name] and [name] and study investigators will meet weekly with research staff to discuss the research study's day-to-day operations, minimize risk, protect participant data's confidentiality, and report adverse events and unanticipated problems. Drs. [name] and [name] and study investigators will ensure and monitor study safety with rigorous training and supervising staff in the field. Participant data will be protected by using unique IDs for all participants and a secure database for data collection.

**Adverse Events**

For the purpose of this protocol, an Adverse Event (AE) is any undesirable or unintended clinical occurrence in a subject that can be attributed to the study intervention. Adverse events may be expected or unexpected. In addition, some AEs may meet the definition of Serious Adverse Event (SAE).

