Led by [name], we will develop an educational series on trauma-informed care to reach the critical health professionals and stakeholders involved in the Houston HVIP development and implementation. As we develop the culture of change, we will implement a series of educational interventions that will be guided by the Kirkpatrick model, an established model of analyzing and evaluating educational programs; we will evaluate the effectiveness of our educational programming at multiple levels. The core levels of the Kirkpatrick model evaluate the learner in their satisfaction of the education (Level 1), change in learning (Level 2), and change in behavior (Level 3) and impact to the population (Level 4).^3,4^ Each assessment of the level of learning will demonstrate the rigor of the educational process and the sustained impact on the learner.

This educational platform will include a series of asynchronous and live educational venues taught by experts in the field to transform the culture at Memorial Hermann Hospital and thus ensure adequate support for the planned intervention. Educational models will be developed by [name], [name], [name], [name], and [name], with core learning objectives of 1) Describing violence and risk factors, 2) Reviewing risk factors for recidivism, and 3) Roles of healthcare and communities to reduce gun violence. [name] will oversee module development to ensure alignment with goals. All educational events will be evaluated via a pre/post-test model (TIC Provider Survey v2.0 - All patient version), with assessments in knowledge, attitude, and behavior around core learning objectives obtained via quantitative surveys utilizing a series of Likert, yes/no, or sliding scaled answers before and immediately post-educational modules. Quantitative analysis will be performed via paired t-test or Chi-squared test, and additional statistical analyses will be used as appropriate.

Within our program, we will focus on identifying victims of firearm violence and presenting them to the Memorial Hermann Hospital at the Texas Medical Center during the study period. We will have two levels of patient support: 1) The Houston-HVIP program (Treatment Intervention) and 2) Standard of care (Comparison Group). Patients will be randomly assigned to either condition, thus supporting the ability to generate causal estimates of each treatment condition of the HVIP program on primary and secondary outcomes.

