**3) Hospitalization or Emergency Department/Urgent Care visits** as a result of mental health (e.g., suicide attempts), substance use (e.g. acute intoxication, acute withdrawal), or violent injury (e.g., gunshot wound, assault injury).
 **4) Severe Emotional Distress**a. patient verbal report of a significant increase in psychiatric symptoms;

b. patients reporting significant distress due to the content of the self-report measures;

c. patients reporting significant distress due to the content of the case management sessions.

d. patients reporting significant distress due to talking about or reliving the experiences of the traumatic event.

Participants will be informed during the consent process and again at the start of each interview that they are free to “skip” any interview question or prompt that makes them uncomfortable and free to end their participation in the interview at any time. They will also be provided with information to contact the study MPIs and UTHealth IRB to discuss any concerns they might have about the study. [name] and [name] and several Co-Is ([name], [name]) have experience conducting these types of interviews with individuals who have a history of trauma. All study staff members who conduct in-depth interviews and interact with the study population will be trained beforehand in trauma-informed care to be sensitive to signs of participant discomfort or distress. Participants will be provided with information about available mental health resources throughout the duration of the study. Available mental health resources and mental health resources at Memorial Hermann Hospital will be made available to all participants.

In each case, the case manager and study staff will consult with the PIs to determine whether the participant’s distress was significant enough to warrant reporting as an AE.

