**Serious Adverse Events**

A Serious Adverse Event (SAE) is any untoward occurrence or effect that:

- Results in death
- Is life threatening
- Requires inpatient unplanned hospitalization or prolongation of existing hospitalization
- Persistent or significant disability/incapacity
- An important medical event that may not result in death, be life threatening, or require hospitalization may be considered an SAE when, based upon appropriate medical judgment, the event may jeopardize the subject and may require medical or surgical intervention to prevent one of the outcomes listed in this definition.

More than one of the criteria above can be applicable to one event.

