**Data Safety Monitoring Board:**

A Data Safety and Monitoring Board (DSMB) will be convened for this study.

The Co-Principal Investigators (PI) will be responsible for ensuring participants’ safety on a daily basis. In addition, the study will impanel a Data and Safety Monitoring Board (DSMB) to act in an advisory capacity to the PI and to evaluate the progress of the study, including periodic assessments of data quality and timeliness, participant recruitment, accrual and retention, participant risk versus benefit, performance of trial sites, and other factors that can affect study outcome.  The DSMB will make recommendations to NINR’s Director concerning the continuation, modification, or conclusion of the trial.

Roles and Responsibilities: The DSMB will review study protocols and provide oversight of recruitment progress, data quality and completeness, efficacy monitoring, and participant safety pertaining to the study. The research team will be responsible for providing study protocols, data, and adverse event reports to the DSMB. All recruitment and data collection will be conducted in Houston, Texas.

DSMB Membership and Affiliations: The DSMB will be comprised of 5 individuals external to the grant to provide safety monitoring and oversight. All members of the DSMB will be external to the grant.

Frequency and Types of Meetings:

The DSMB will meet annually (at a minimum) via teleconference to review the study progress, data quality, and participants' safety.  During these meetings, the PIs and Co-Is will provide the DSMB with an update on study recruitment and enrollment, the progress of participants within the study, and the presence of all AE/SAE, including classifications based on severity, expectedness, and relatedness to study procedures.  The DSMB will then have private discussions and provide recommendations as appropriate.

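### The adverse event definition requires attribution to the study intervention, which contradicts the protocol's own expected-event list, serious event definition and later relatedness classification

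*Protocol*

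**What the plan says.** The governing definition, given for use throughout the protocol, is in the section Adverse Events: "an Adverse Event (AE) is any undesirable or unintended clinical occurrence in a subject that can be attributed to the study intervention". The same section introduces serious events as a kind of adverse event, noting that "some AEs may meet the definition of Serious Adverse Event (SAE").

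Four other places bear on it:

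- **Expected Adverse Events.** Six categories are listed. Item 3 is "Hospitalization or Emergency Department/Urgent Care visits" arising "as a result of mental health (e.g., suicide attempts), substance use (e.g. acute intoxication, acute withdrawal), or violent injury (e.g., gunshot wound, assault injury"). Other items cover loss of confidentiality through data collection, retaliation risk, emotional distress (including distress from the questionnaires), suicidal ideation and psychological discomfort.
- **Serious Adverse Events.** The definition opens "A Serious Adverse Event (SAE) is any untoward occurrence or effect that" and continues with the usual seriousness criteria. It does not mention attribution.
- **Recording and Reporting Adverse Events.** Staff decide at each evaluation whether an adverse event has occurred, and every adverse event from enrollment to exit is to be documented. The principal investigators have the final say on whether an event counts as adverse or serious.
- **Data Safety Monitoring Board.** The investigators present all adverse and serious events, "including classifications based on severity, expectedness, and relatedness to study procedures". The section Data and Safety Monitoring separately has the board assess the relationship of events to the study.

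**The concern.** In a randomized trial, adverse event data show whether one arm has more untoward events than the other. That requires events to be counted the same way in both arms, with causality judged afterwards. Here causality is judged first, and an event that fails the test is not an adverse event.

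The test is also uneven across arms. The Study Design section describes the two levels of support as "1) The Houston-HVIP program (Treatment Intervention) and 2) Standard of care (Comparison Group"). A participant assigned to standard of care does not receive the Houston-HVIP program, so a harm in that arm can hardly be attributed to it. At stake are the completeness of non-serious adverse event reports and the meaning of any difference in counts between arms. The investigators rely on the board to identify events that would lead to a halt, modification or termination, and the research team supplies the reports on which it does so.

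**Working it through.** No figure in the plan can be reproduced here, because the point concerns a definition. The check sets the sections side by side.

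1. **Definition taken alone.** Two conditions must hold: an undesirable or unintended clinical occurrence, and attribution to the study intervention. With Houston-HVIP as the intervention, unattributed events in either arm fail the second condition, and so do nearly all standard-of-care events.

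2. **Recording rule.** The instruction to document all adverse events has no arm restriction. It uses the defined term, however, and so inherits the attribution condition.

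3. **Expected-event list.** An expected event is defined as a type of adverse event, so the list formally sits inside the definition. Its content does not fit there.
   - Item 3 covers hospital and emergency visits for violent injury, suicide attempts and intoxication. These are background risks of this population in both arms, and no attribution is asked for.
   - Confidentiality loss from data collection and distress from the questionnaires arise from study procedures common to both arms, not from the intervention.
   - For severe distress and suicidal ideation, the stated reporting test is whether the distress is significant enough. That is a severity test, not a causality test.

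4. **Serious events.** On its own wording, the serious event definition takes in any overnight unplanned admission, related or not. If serious events are a subset of adverse events, as the Adverse Events section suggests, an unrelated admission is excluded. The text does not settle which reading applies. An emergency visit without an overnight stay generally does not meet the hospitalization criterion, so its capture depends mainly on the adverse event definition.

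5. **Relatedness.** Both monitoring sections classify relatedness after an event is reported. If every reported event is attributable by definition, that field has little left to distinguish.

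6. **Who applies the filter.** Staff named for the determination are the case manager, the program manager and a graduate research assistant. The Randomization Procedure section says case managers know the assignment. The principal investigators decide finally; the protocol does not state whether they are blinded.

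7. **Illustration of scale.** Inputs from Sample Size and Statistical Power are a one-year probability of firearm violence of 42% under standard of care and 137 participants in that arm. Expected control participants with such an event: 0.42 x 137 = 57.5, about 58. Under the definition alone, essentially none of these is an adverse event. Under item 3, every one that leads to an emergency visit or admission is. The 58 is an upper bound for firearm events reaching hospital, because the composite also counts self-reported victimization without hospital care. It excludes visits for non-firearm assault, mental health or substance use. It shows how much depends on the choice of section and does not estimate bias.

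**The case against.** The best defence is that the specific rules override the general definition in practice. The expected-event list names events that occur in either arm, the serious event definition stands without attribution, and recording runs from enrollment to exit for everyone. Staff working from the list would log many standard-of-care events. In addition, relatedness to study procedures is broader than attribution to the intervention, so that classification is not wholly redundant.

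A reader might go further than the text allows and infer that the monitoring board cannot compare the arms, that control-arm counts must approach zero, or that an excess of retaliation, distress or suicidality could not be recognised. The documents do not support these readings:

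- Baseline and follow-up measures flag suicidality and retaliation risk with no restriction by arm.
- Repeat firearm violence, wider violent reinjury, PTSD and aggression are trial outcomes in both arms. Injuries and deaths are also taken from hospital and death records.
- The board receives other safety data besides adverse events. Display by arm may be set out in its charter or in the detailed monitoring plan, neither of which is shown, so its absence from the protocol is no finding.
- Personnel who collect or evaluate outcome data are blinded, so it would be wrong to describe the whole team as unblinded.

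All of this limits the consequence. It does not remove the contradiction: the defence works only if staff disregard the definition that the protocol tells them to use.

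**Conclusion.** The definition is wrong as written and inconsistent with the rest of the safety text. Followed literally, it removes unattributed harms and most non-serious standard-of-care harms from adverse event reports. It also leaves open whether an unrelated hospitalization is a serious event. Because the filter acts at the reporting step, partly through unblinded case managers, adverse event counts could differ between arms without any difference in true harm.

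The direction on the literal reading is under-counting in the standard-of-care arm. The amount cannot be derived from the protocol, because it depends on which section staff follow. The conclusion assumes that the study intervention means the Houston-HVIP program, as the Study Design section labels it. Confidence is high for the contradiction and lower for its practical effect, given the other routes by which harms are captured. The change should be made.

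A minor related point: Data and Safety Monitoring says "No physical or psychological adverse effects of the intervention are known or anticipated", while item 4c of the expected list names distress caused by the content of case management sessions. The tension is with that sub-item. Most of the other listed events are tied to the study or the population rather than to the intervention, so the list as a whole does not contradict the statement.

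**What to change.** - In Adverse Events, define an adverse event as any untoward occurrence in a participant in either arm from enrollment to exit, whether or not considered related to the intervention or study procedures.
- Record relatedness as a separate field, completed for both arms.
- Align Expected Adverse Events, Serious Adverse Events and Recording and Reporting Adverse Events with that wording, so that an unrelated hospitalization has one clear classification.
- Reconcile the statement in Data and Safety Monitoring that no adverse effects of the intervention are anticipated with item 4c of the expected list.

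The cost is a short protocol amendment and one field on the adverse event form. More events will be logged, most of them unrelated, which adds work for staff and for the board. Treatment, endpoints and sample size are unaffected.
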